### Trial duration and criteria for early study termination

Patient accrual is estimated to be finished within 2 years, with a follow-up period of 1 year after last patient in. The clinical trial should be concluded 3 years after first inclusion. Early termination of the trial will occur if the toxicity of this extreme hypo-fractionated SBRT is determined to be unacceptable (≥ grade 3 in more than four of the first ten patients for acute or more than 20% of all patients for chronic side effects). The study can be terminated early, if a) the hypothesis of the study can be answered by new data, b) the understanding of the radiobiology for prostate cancer is markedly altered by new data, or c) the recruiting target is not met during the recruitment phase.

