### Study design

The HYPOSTAT study is designed as a prospective observational trial. The hypothesis is that image-guided SBRT with 35 Gy in 5 fractions (7 Gy per fraction) is feasible in the treatment of prostate cancer. The primary endpoint is toxicity to the GI and GU system at 1 year after treatment assessed according to the Common Terminology Criteria for Adverse Events (CTCAE v. 4.0) and Radiation Therapy Oncology Group (RTOG) Scores. Secondary endpoints are PSA-failure-free survival, relapse-free survival, urological function assessed by the International Prostate Symptom Score (IPSS), and Quality of life (QoL) assessed before and after treatment with the European Organization for Research and Treatment of Cancer (EORTC) Quality of Life Questionnaire (QLQ) C30 and the Patient Oriented Prostate Cancer Utility Scale (PORPUS) questionnaire.

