### Treatment planning and delivery

Treatment will be carried out with a robotic CyberKnife system (Accuracy Inc., USA) using real-time tracking. Three to four fiducial markers will be necessary to identify the location of the prostate during treatment. The distance between two fiducial markers should be ≥ 2 cm. Implantation of fiducial markers should be completed at least 5 days before treatment-planning computed tomography (CT) to reduce the post-implantation migration of the fiducial marker. During planning CT, and on any treatment day, the use of an enema is advised to reduce the maximum rectal diameter. A bladder catheter is not necessarily needed, but a consistent and constant bladder filling of 20–30 ml during planning CT and treatment is recommended.

Gross tumor volume (GTV) is defined as the prostate on the planning magnetic resonance imaging (MRI) for patients with a low-risk profile and as the prostate with the bases of seminal vesicles (1 cm proximal) for all other patients. The clinical tumor volume (CTV) is defined as GTV plus 1–2 mm for patients with low-risk prostate cancer and plus 2 mm for all other patients. The planning target volume is defined as CTV plus an anisotropic margin of 1 mm posterior into the direction of the rectum and 3 mm in all other directions. Organs at risk (OAR) are rectum, bladder, urethra (if identifiable), neurovascular bundles (if identifiable), penile bulb, small bowel, femoral heads and the skin (5 mm thick). The rectum is defined from the inferior level of the anus to the recto-sigmoid junction to give a length of approximately 12 cm.

All patients will be treated with 35 Gy in 5 fractions (7 Gy per fraction) prescribed to the 80–85% isodose (maximum dose = 100%) covering the PTV to 95% (PTV_35Gy_ ≥ 95%). OAR dose limitations (Table 1) are specified according to published guidelines [33–45, 53–56] and the urethral dose reduction technique will be used to minimize risks of side effects [57]. Patients will be treated every second day with a minimum of 36 h between two fractions. The treatment time shall be 1.5 to 2 weeks.

**Table 1 Tab1:** Dose limits for organs at risk relevant for prostate radiosurgery

Organ at risk	Dose limit
Rectum	D_max_ < 38 Gy V_36Gy_ < 1 cm^3^ & < 5% V_29Gy_ < 15 cm^3^ & < 20% V_18Gy_ < 25 cm^3^ & < 50%
Bladder	D_max_ < 38 Gy V_36Gy_ < 10 cm^3^ & < 10% V_18Gy_ < 40%
Urethra	D_max_ < 44 Gy
Penile Bulb	V_30Gy_ < 3 cm^3^ & < 50%
Femoral Heads	V_30Gy_ < 10 cm^3^ V_14,5Gy_ < 5%

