### Follow-up assessments

The primary endpoint will be the feasibility of extreme hypo-fractionated SBRT in the treatment of prostate cancer assessed 1 year after treatment, as all of the acute and certain intermediate toxicity will be observed in this period. Follow-up visits will occur at 4–6 weeks, 3 months (± 1 week), 6–9 months and 12–15 months after the last day of irradiation. During follow up, side effects will be documented (if any) and the PSA value (at least twice), IPSS and QoL using the PORPUS questionnaire will be documented. The course of the PSA value will be used to declare biochemical failure according the Phoenix definitions. In case of failure to identify disease progression by assessing the PSA value, progression events are defined as radiologically documented disease progression using Response Evaluation Criteria In Solid Tumors (RECIST) Criteria (Revised Guidelines, Version 1.1, 2009). QoL is assessed using the EORTC QLQ C30 questionnaire at the last follow-up visit.

The reasoning for this short follow-up time was due to the nature of the study design being a feasibility trial with a single technique which would serve as the basis for a subsequent multi-institutional multi-platform trial with long term follow-up. I.e., we did not want to overly delay such long term multi-institutional multi-platform study and decided to finish the initial feasibility trial as soon as possible. For long-term evaluation, patients will of course be followed for at least 5 years according to the standard practice for radiotherapy in Germany which additionally will include treatment relevant efficacy, side effects, IPSS and QoL assessments; however, this will not be part of the study protocol.

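### The planned close, one year after the last patient enters, comes before the last-enrolled patients can reach the 12–15 month visit that records the primary endpoint

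*Protocol article*

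**What the plan says.** Four statements in the protocol article bear on the timetable.

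- **Study design** sets the endpoint: "The primary endpoint is toxicity to the GI and GU system at 1 year after treatment".
- **Follow-up assessments** gives the last two study visits as "6–9 months and 12–15 months after the last day of irradiation". The EORTC QLQ-C30 is due at the last of these. Routine follow-up of at least 5 years continues afterwards, but the section states that it lies outside the study protocol.
- **Treatment planning and delivery** puts time between inclusion and the last fraction: "The treatment time shall be 1.5 to 2 weeks". It also asks for at least 5 days between marker implantation and the planning CT.
- **Trial duration and criteria for early study termination** sets the calendar: "Patient accrual is estimated to be finished within 2 years", "with a follow-up period of 1 year after last patient in". It adds: "The clinical trial should be concluded 3 years after first inclusion".

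**The concern.** The calendar counts from inclusion, while the visit schedule counts from the last day of irradiation. A patient included at the end of accrual must still be planned and treated before the follow-up clock starts. A close one year after that inclusion therefore falls before the 12-month mark, and more than three months before the window ends.

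What is at stake is completeness. If the calendar were followed literally, the last-enrolled patients would have no in-study primary assessment at 1 year and no final-visit QLQ-C30. The loss would come from the timetable itself, so it is avoidable.

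**Working it through.** **Inputs from the article:** accrual 24 months; follow-up after the last inclusion 12 months; primary visit 12 to 15 months after the last irradiation; treatment 1.5 to 2 weeks (10.5 to 14 days); at least 5 days from markers to planning CT; 85 patients.

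**Assumptions:** uniform accrual, 85/24 = 3.54 patients per month; one month = 30.44 days. The article does not give the total time from inclusion to the last fraction. The documented minimum is 10.5 days (treatment only, markers already placed). With 2 weeks of treatment and 5 days after marker placement it is 19 days. A lag of 3 to 6 weeks is an assumption, shown for sensitivity.

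**The plan's own figure:** 24 + 12 = 36 months, which reproduces the stated 3 years and leaves no slack.

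**Formulas,** with lag L in months:
- time since irradiation of the last patient at close = 12 − L
- patients who cannot reach month 12 = 3.54 × L
- patients whose window is not fully inside the trial = 3.54 × (3 + L)
- duration needed = 24 + L + 12 (visit at month 12) to 24 + L + 15 (visit at month 15)

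| Lag | L (months) | Last patient at close (months past irradiation) | Cannot reach month 12 | Window not fully inside | Duration needed (months) |
|---|---|---|---|---|---|
| 10.5 days (documented) | 0.34 | 11.7 | 1.2 | 11.8 (13.9%) | 36.3 to 39.3 |
| 19 days (documented) | 0.62 | 11.4 | 2.2 | 12.8 (15.1%) | 36.6 to 39.6 |
| 3 weeks (assumed) | 0.69 | 11.3 | 2.4 | 13.1 (15.4%) | 36.7 to 39.7 |
| 6 weeks (assumed) | 1.38 | 10.6 | 4.9 | 15.5 (18.2%) | 37.4 to 40.4 |

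On the documented intervals, the last patient misses the earliest permitted visit by 10.5 to 19 days and the end of the window by about 3.3 to 3.6 months. The fifth column includes the patients in the fourth. The difference, 3 × 3.54 = 10.6 patients, have a window that opens before the close and ends after it, so they can still be seen in window if the visit is booked early enough.

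**Effect on power.** Exact binomial, lower tail, one-sided 0.025, with the printed rates. Here n = 83 is the loss of 2 patients, and n = 72 the extreme case in which all 13 with an incomplete window are lost.

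| n | GU, 17.5% against 2.8% | GI, 10% against 1.1% |
|---|---|---|
| 85 | 99.7% | 98.5% |
| 83 | 99.8% | 93.6% |
| 72 | 99.6% | 95.5% |

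The GI values move unevenly because the cut-off is a whole number (3 events at n = 85, 2 at n = 83 and n = 72). All stay above the 88% that the article gives for GI with 54 patients.

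**The case against.** The strongest reply is that the duration section is planning language. Accrual is estimated and the conclusion is what should happen. Nothing says that open patients are censored or that data are locked at month 36. The visit schedule is the firmer statement, and one year may be a rounded form of the same endpoint. The article is also a condensed text, and a formal end-of-trial definition may stand in the full protocol. This lowers the seriousness, but it does not reconcile two timelines that the article itself prints.

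A second reply is that the last patient in could loosely mean the end of that patient's treatment. A visit at exactly month 12 would then just fit, but the other three months of the window would not. Faster accrual does not help either, because follow-up is tied to the last inclusion. Slower accrual would make the 3-year limit bind harder.

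Three stronger readings are tempting, and the document does not support them:

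- **That 12 to 16 patients lose their primary outcome.** Most of them can be seen at month 12 or soon after, in window and before the close. Only those included in roughly the last 2 to 3 weeks of accrual are strictly out of reach on the documented intervals.
- **That losing even one patient costs substantial power.** A reader might infer this because the printed 78% at n = 85 is matched by a GU null of 10% (78.5%), where the cut-off falls from 3 events to 2 at n = 84. The article prints 17.5% for GU, and at that null power hardly moves. That the printed GU power does not reproduce at 17.5% is a separate matter.
- **That the result is biased towards low toxicity, or that 85 lacks a dropout allowance.** The first cannot be sized from the document: few patients lose a few weeks, and the earlier visits still record side effects. The second is commonly left to the full protocol or analysis plan.

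**Conclusion.** The inconsistency is real and minor. As written, the trial closes before the last-enrolled patients can have the visit that records the primary endpoint. On the documented intervals the last patient is 11.4 to 11.7 months past irradiation at close. Under assumed uniform accrual about 1 to 2 of 85 patients cannot reach month 12, or about 2 to 5 if the lag is 3 to 6 weeks. The counts depend on these accrual and lag assumptions. The shortfall itself does not, since it exists for any lag above zero when the clock starts at inclusion. The harm is avoidable incompleteness of the primary outcome and the final QLQ-C30 in the last patients, not loss of power.

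**What to change.** In the duration section, replace the two calendar rules by one event-based rule: the trial remains open until the last treated patient has completed the 12–15 month visit, and the primary analysis follows that visit. The year counts can stay as estimates, restated as about 36.3 to 40 months after first inclusion if accrual takes 24 months. If the full protocol already defines the end of the trial in this way, the duration text only needs to be aligned with it.

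The cost is a wording amendment and about 0.3 to 4 more months before the final analysis, depending on the lag and on when in the window the last visit takes place. The visit schedule, treatment and sample size are unchanged.

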### Ethical and legal considerations

The HYPOSTAT study protocol was reviewed by the ‘Independent Expert Committee of the DEGRO’ and an approval from the National Radiation Protection Authority (BfS) for conducting the study was deemed necessary. The study was approved by the BfS (reference number Z5–22463/2–2013-031) and by the independent ethics committee of the University of Luebeck (reference number 13–052) and, subsequently, by the ethics committees responsible for the participating clinics and institutions (University of Kiel, University of Frankfurt and University of Rostock). The HYPOSTAT study is accredited by the Radiation Oncology Working Group (ARO) of the German Cancer Society. The registration number at clinicaltrials.gov is NCT02635256. The study is monitored and audited by the center for clinical trials (ZKS Luebeck, Germany, protocol number ZKS-121-003). Sponsor of the study is the University Medical Center Schleswig Holstein, and the study is partly financed by the Dr.-Rurainski-Stiftung (Ettlingen, Germany) and the Saphir Medical Engineering Group GmbH (Guestrow, Germany).

## Discussion

The HYPOSTAT trial aims at demonstrating short term feasibility of extreme hypo-fractioned SBRT for the treatment of prostate cancer and might be used as the pilot study for a multi-center multi-platform or for randomized-controlled trials in Germany comparing conventional radiotherapy with SBRT for localized prostate cancer in the future. The study concept of patient enrollment, follow-up and evaluation by multiple public university medical centers and actual patient treatment in dedicated private radiosurgery practices with high-tech radiation equipment is unique for clinical trials.

## Abbreviations

BfS: Bundesamt fuer Strahlenschutz (National Radiation Protection Authority)
CT: Computer Tomography
CTCAE: Common Terminology Criteria for Adverse Events
CTV: Clinical Target Volume
DEGRO: Deutsche Gesellschaft fuer Radioonkologie (German Society for Radiation Oncology)
EBRT: External Beam Radiation Therapy
EORTC: European Organization for Research and Treatment of Cancer
GI: Gastrointestinal
GTV: Gross Target Volume
GU: Genitourinary
HYPOSTAT: Hypofraktionierte Strahlenchirurgie bei lokal begrenztem Prostatakarzinom (Hypo-fractioned radiosurgery for localized prostate cancer)
IMRT: Intensity Modulated Radiation Therapy
IPSS: International Prostate Symptom Score
MRI: Magnetic Resonance Imaging
NCI: National Cancer Institute
OAR: Organ at Risk
PORPUS: Patient Oriented Prostate Cancer Utility Scale
PSA: Prostate Specific Antigen
PTV: Planning Target Volume
QLQ: Quality of Life Questionnaire
QoL: Quality of Life
RECIST: Response Evaluation Criteria In Solid Tumors
RTOG: Radiation Therapy Oncology Group
SBRT: Stereotactic Body Radiation Therapy
VMAT: Volumetric Modulated Radiation Therapy
